**Visit 6 – FOLLOW-UP VISIT/END OF STUDY, age of 9 months (Infant aged 36  $\pm$  2 weeks)**

- Subjects will be brought to the vaccine trial clinic.
- Continued consent to participate in the study will be confirmed.
- An interim medical history will be taken.
- Physical examination including vital signs (temperature, respiratory rate, pulse rate), and anthropometry (weight, mid left upper arm circumference (MUAC), length) will be performed by the research field worker / research nurse.
- The injection site will be inspected by the research physician and findings documented in the CRF.
- Adverse events (local and systemic) that may have occurred since the last visit and any concomitant medications will be documented in the CRF.
- 5 mL of blood will be collected for immunogenicity of MVA.HIVA and HLA typing.
- EPI vaccines appropriate for age and study group will be given (measles vaccine, yellow fever, OPV)
- Any child that was HIV antibody positive at 28 weeks of age will be re-tested. If the test remains positive they will be given an appointment for repeat testing every 6 months until they become HIV antibody negative.
- Parents will be told that their babies have graduated from the study. Study sticker will be removed from their health cards and children will continue to be offered free health care at Sukuta Health Centre until 3 years of age.

**CONFIDENTIAL**

## **7 STUDY INTERVENTION / INVESTIGATIONAL PRODUCT**

### **Study Product Acquisition**

Study product will be shipped by IDT Biologika GmbH, [name] directly to the trial site.

### **Formulation, Packaging and Labelling**

MVA.HIVA is manufactured to Good Manufacturing Practice conditions by Impfstoffwerk Dessau-Tornau (IDT), Germany, as contracted by UK's Medical Research Council. It is supplied as a ready to use solution in glass vials. These vials are labelled as containing MVA.HIVA in accordance with good manufacturing practice guidelines on investigational medicinal products.

### **Product Storage and Stability**

MVA.HIVA will be stored in an allocated freezer at or below  $-20^{\circ}\text{C}$  in the locked freezer room at MRC Fajara. On the day of administration it will be placed in a cold box containing dry ice and transported to the study site where it will be stored in the cold box until thawing for use. The study physician will be in custody of the box at all times.

### **Preparation, Administration and Dosage of Study Intervention/Investigational Product**

The batch of the vaccine, MVA.HIVA, will be provided in vials of 200  $\mu\text{l}$  at a concentration of no less than  $5 \times 10^8$  pfu/ml in 10 mM Tris buffer, 0.9% NaCl. The dose of MVA.HIVA to be used in this stage will be  $5 \times 10^7$  pfu.

On the vaccination day, vaccines will be transported to Sukuta Health Centre in a cold box containing dry ice. It will be allowed to thaw to room temperature before use, and administered within 60 minutes of thawing. One vaccine vial per subject to be vaccinated will be used. The vaccine will be administered intramuscularly over the deltoid region of the left arm (the usual site of BCG vaccination). The physician will draw up the vaccine and the volume drawn will be checked and signed for onto the CRF by the physician and one other member of staff at Sukuta Health Centre (physician / nurse or field worker). The physician will wear gloves and eye protection when drawing up and administering the vaccine. Subjects will stay in the health centre for observation for at least 60 minutes after vaccination. During administration of the vaccines, medicines and resuscitation equipment will be immediately available for the management of anaphylaxis.

In order to minimise dissemination of the recombinant vectored vaccine virus into the environment the inoculation site will be covered with a dressing 10 minutes after immunization. This should absorb any virus that may leak out through the needle track. The dressing will be removed from the injection site at the end of the 60 minute observation period and will be disposed as GMO waste by autoclaving and incineration, in accordance with the relevant SOP and current standard practice at MRC, The Gambia.

## **8 ASSESSMENT OF SCIENTIFIC OBJECTIVES**

### **Specification of the Appropriate Outcome Measures**

## **CONFIDENTIAL**

### **Primary Outcome Measures**

- The safety of MVA.HIVA will be determined by analysis of adverse events, reactogenicity, biochemical and haematological data that will be actively collected.
- Assessment of the immunogenicity of a single dose of MVA.HIVA (administered 4 weeks after the last EPI vaccines to healthy infants who have been vaccinated with BCG) by measuring the frequency of IFN- $\gamma$ -producing cells following stimulation with pooled 15-mer peptides derived from the HIVA immunogen in *ex-vivo* (effector) and 10-day cultured (memory) ELISPOT assays.

### **Secondary**

- Determination of gross interference of MVA.HIVA with the immunogenicity of DTwPHib, HepB, OPV and PCV-7 vaccines will be through comparing actively collected data on antibody levels to the antigens contained in these EPI vaccines in the vaccine and control groups. Historical data from other studies in the same population may also be used to provide normal ranges.
- If there are any residual PBMCs after the IFN- $\gamma$  ELISPOT assays have been performed, other immunological assays may be performed, which might include:
  - ELISPOT assays for interleukin 2 and tumour necrosis factor alpha
  - T cell proliferation to HIVA peptides
  - T cell depletion assays
  - Cytokine detection using ELISA/LUMINEX
  - Intracellular cytokine staining and multicolour flow cytometric analysis

## **9 ASSESSMENT OF SAFETY**

All adverse events (AE) occurring in participants after administration of vaccine will be documented and reported as described below.

### **9.1 Definitions**

#### **Adverse Event**

An AE is any untoward medical occurrence, including a dosing error, which may occur during or after vaccination. The AE may or may not have a causal relationship with vaccination as indicated by physical signs, symptoms, and/or clinically significant laboratory abnormalities that occur. The definition includes intercurrent illnesses, injuries, exacerbation of pre-existing conditions, and events occurring as a result of product misuse or overdose.

A change in a laboratory variable is considered an AE if it leads to a change in the subject's functional status or if it is considered by the attending physician to be

## **CONFIDENTIAL**

clinically significant. The following laboratory parameters will be monitored during the course of this study (as previously outlined): full blood count (FBC), creatinine and ALT.

Expected local reactions to the vaccine will not be recorded as an adverse event, but will be recorded on the CRFs. These include:

- Redness
- Induration
- Scaling / Blistering / Ulceration
- Axillary lymph node enlargement
- Pain (scored as follows)
  - 0 No pain
  - 1 Painful to touch
  - 2 Partial restriction of activities
  - 3 Unable to use the arm

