### **2.3 Potential Risks and Benefits**

#### **2.3.1 Potential Risks**

The general risks to participants in this Phase 1 study are associated with phlebotomy and with vaccination. The total volume of blood drawn over the study period (20 mL) should not compromise these otherwise healthy infants. It is important to note that MVA has been administered to over 120,000 subjects as part of the smallpox campaign with no serious adverse reactions, and therefore has a good safety record. Potential risks include the following:

**Local reactions:** Mild tenderness and bruising may result from venepuncture. An inflammatory reaction as manifested by redness, swelling, scaling and/or tenderness may occur at the site of vaccine injection. In previous studies with MVA.HIVA, these local reactions resolved spontaneously within a couple of days.

**Systemic signs and symptoms:** Systemic events following administration of MVA as a vector that could potentially occur include a flu-like illness with low-grade fever, chills and malaise. As with any other vaccine, temporary ascending paralysis, the Guillain-Barré syndrome (GBS) or immune mediated reactions that can lead to organ damage may occur. For influenza vaccines an excess of approximately 1 GBS case per million persons immunized has been observed. No cases were observed in people under 45 years of age. However, GBS has never been known to be caused by any recombinant MVA or vaccines containing any of their components.

**Allergic Reactions and Anaphylaxis:** As with any vaccine, allergic reactions are possible.

All subjects will be closely monitored and followed up.

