### **Serious Adverse Event (SAE)**

Any AE (whether or not considered related to the investigational product) that results in any of the following outcomes is defined as an SAE.

- 1) Death (i.e. death from any cause at any time)
- 2) Life-threatening event (i.e. the subject was, in the view of the investigator, at immediate risk of death from the event that occurred). This does not include an AE that, if it occurred in a more serious form, might have caused death.
- 3) Persistent or significant disability or incapacity (i.e., substantial disruption of one's ability to carry out normal life functions).
- 4) Hospitalisation: regardless of length of stay, even if the hospitalization is a precautionary measure for continued observation. Hospitalisation (including inpatient or outpatient hospitalization for an elective procedure) for a pre-existing condition that has not worsened unexpectedly does not constitute a serious AE.
- 5) An important medical event (that may not cause death, be life threatening, or require hospitalization) that may, based upon appropriate medical judgment, jeopardize the subject and/or require medical or surgical intervention to prevent one of the outcomes listed above. Examples of such medical events include allergic reaction requiring intensive treatment in an emergency room or clinic, blood dyscrasias, or convulsions that do not result in inpatient hospitalization.

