## **9.2 Adverse Events Assessment**

For every adverse event (AE), an assessment of the relationship of the event to the administration of the vaccine will be undertaken. A related AE refers to an AE for which there is a possible, probable or definite relationship to administration of a vaccine. The investigator will make interpretation of the causal relationship of the intervention to the AE in question. This interpretation will be based on the type of event, the relationship of the event to the time of vaccine administration,

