#### **Methods and Timing for Assessing, Recording, and Analyzing Safety Parameters**

The following scale will be used to assess the severity of all AEs:

- 0 = Absence of the indicated symptom
- 1 = Mild (awareness of a symptom but the symptom is easily tolerated)
- 2 = Moderate (discomfort enough to cause interference with usual activity)

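### Section 9.1 keeps listed local reactions out of adverse event recording with no seriousness limit, so a serious one has no stated route into SAE reporting or the SAE count

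*Protocol*

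**What the plan says.** Under Adverse Event, section 9.1 opens with a broad definition: "An AE is any untoward medical occurrence, including a dosing error, which may occur during or after vaccination". It then takes one class out of AE recording: "Expected local reactions to the vaccine will not be recorded as an adverse event, but will be recorded on the CRFs". Five entries follow: redness; induration; "Scaling / Blistering / Ulceration"; axillary lymph node enlargement; and pain, scored 0 to 3, where the top score is loss of use of the arm. No entry carries a threshold of size, severity or outcome.

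The next definition in section 9.1 builds SAEs on AEs: "Any AE (whether or not considered related to the investigational product) that results in any of the following outcomes is defined as an SAE". Section 9.2 does the same for causality: "For every adverse event (AE), an assessment of the relationship of the event to the administration of the vaccine will be undertaken". Section 9.3 does so for grading: "The following scale will be used to assess the severity of all AEs".

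Section 6.2, Visits 5 and 6, tells staff to document adverse events of both local and systemic kind. Section 8 and section 11.2.1 place reactogenicity beside adverse events in the safety assessment.

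**The concern.** Recording local reactogenicity apart from other AEs is a legitimate choice. It normally comes with a clause that returns a reaction to AE and SAE handling once it becomes serious, and section 9.1 has none. The list reaches into severe territory on its face. Its top pain score describes loss of function, much as grade 3 of the general scale does, and ulceration is included without limit.

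Two things are at stake. The first is expedited oversight, because the report to the sponsor and Local Safety Monitor is triggered by an SAE. The second is the SAE count, which section 4.1 names as one measure of safety and which Table 3 turns into an interval. Staff could also file the same ulcer as an AE under Visit 5 or only as a CRF reactogenicity entry under section 9.1, so the count would depend on who completed the form.

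**Working it through.** **1. Which steps depend on AE or SAE status**

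| Step | Where | Applies to |
|---|---|---|
| SAE status | 9.1 | AEs with a serious outcome |
| Causality assessment | 9.2 | every AE |
| Follow-up to resolution | 9.2 | all AEs |
| Report within 24 hours to sponsor and Local Safety Monitor | 9.2 | SAEs |
| Immediate Local Safety Monitor review, power to suspend enrolment | 9.3 | SAEs |
| Severity scale 0-4 | 9.3 | all AEs |

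A listed reaction not recorded as an AE enters none of these rows, and no sentence returns it if it meets a seriousness criterion.

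**2. Where the text points the other way**

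The opening AE definition has no exception and would cover an ulcer or an enlarged node. Visits 5 and 6 ask for local events as AEs. Both conflict with the recording rule, and nothing says which prevails.

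**3. What is still measured for each listed reaction**

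| List entry | Measure stated |
|---|---|
| Redness | largest diameter (Visits 3, 4, 5) |
| Induration | largest diameter (Visits 3, 4, 5) |
| Scaling, blistering, ulceration | none |
| Axillary node enlargement | none |
| Pain | score 0-3 |

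Three of five entries keep a measure of size or severity and two have none. All five lose the common 0-4 scale.

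**4. Effect of one event on Table 3**

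Table 3 reproduces with the Wilson score interval, with n = 24, z = 1.96 and z² = 3.84:

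limits = [p + z²/(2n) ± z√(p(1−p)/n + z²/(4n²))] / (1 + z²/n)

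- 0/24: the lower limit is 0 and the upper limit reduces to z²/(n + z²) = 3.84/27.84 = 13.8%. Table 3 gives 0.0-13.8%.
- 1/24: p = 0.0417. The centre is (0.0417 + 0.0800)/1.160 = 0.1049. The half-width is 1.96 × √(0.001664 + 0.001667)/1.160 = 0.0975. The limits are 0.7% and 20.2%. Table 3 gives 0.7-20.2%.

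If one vaccinee had a listed reaction leading to admission and it were recorded only as reactogenicity, the SAE rate would be 0 instead of 1/24 = 4.2%. The upper limit would be 13.8% instead of 20.2%, a difference of 6.4 percentage points. The event is assumed for illustration, as the documents give no probability for it.

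**The case against.** The strongest reply is that section 9.1 states a recording rule and does not redefine an AE. A hospitalised infant would still meet the broad definition, and SAE criterion 4 covers admission of any length, so a sensible investigator would report it. That is a fair reading, but it needs staff to override an explicit instruction. It shows that the text is contradictory and does not supply the missing clause.

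Several stronger inferences are tempting and are not supported:

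- **Local reactions drop out of the safety evaluation.** They do not. They are recorded on the CRF, the site is inspected by the research physician at Visits 4 to 6, and reactogenicity is part of the primary safety outcome (section 8) and the group comparison (section 11.2.1). Only AE and SAE counts and expedited reporting are affected.
- **Only pain is graded.** Redness and induration are measured by diameter.
- **The rule disables halting.** A SUSAR must be unexpected (section 9.2), so it is the label expected, not the AE recording rule, that takes these reactions outside the automatic suspension. The DMEC may also suspend or stop on any grounds, and the Local Safety Monitor may call a meeting whenever needed.
- **Blistering, ulceration and node enlargement are wrongly called expected.** Section 2.3.1 says only "An inflammatory reaction as manifested by redness, swelling, scaling and/or tenderness may occur at the site of vaccine injection", but its list is introduced as inclusive rather than complete, and the text of section 2.2.5 on adult safety was not available to me. A mismatch with section 2.3.1 can be noted, and no more.
- **Local reaction is the most likely serious harm.** No section says so. Section 2.3.1 reports that earlier local reactions resolved within days.

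**Conclusion.** Wrong as written, within a narrow scope. The exclusion in section 9.1 has no seriousness limit, and it contradicts the AE definition in the same section and Visits 5 and 6. A listed reaction that meets a seriousness criterion therefore has no stated route into causality assessment, SAE reporting, Local Safety Monitor review or the Table 3 count. Two of the five list entries also have no grade or measurement. The protocol leaves open whether a reaction stays expected however severe it becomes.

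The size depends on an event that may never occur. With 24 vaccinees, a single one changes the SAE result from 0/24 to 1/24. The conclusion assumes that staff follow the recording rule literally and that no SAE form or site procedure outside the protocol supplies the missing clause. A reader might infer that the overall safety conclusion is biased towards safe. The documents do not support that, because the same reactions are analysed as reactogenicity.

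**What to change.** Keep the separate recording of local reactogenicity, with three changes:

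1. In section 9.1, add that any listed local reaction meeting one of the SAE criteria is an AE and an SAE, and is assessed, reported and counted as such.
2. Add a severity grade on the CRF for scaling, blistering or ulceration and for axillary node enlargement.
3. Reconcile section 9.1 with Visits 5 and 6 in section 6.2 and with the SUSAR text in section 9.2, so that one rule says when a local reaction is an AE. State whether the label expected holds regardless of severity, and check the list against section 2.3.1.

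The cost is a few sentences and a few CRF fields. The reported AE or SAE count in Group 1 may be higher. Tabulating all local reactions together with the AEs is a matter of presentation and is not needed.

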### **Serious Adverse Event (SAE)**

Any AE (whether or not considered related to the investigational product) that results in any of the following outcomes is defined as an SAE.

- 1) Death (i.e. death from any cause at any time)
- 2) Life-threatening event (i.e. the subject was, in the view of the investigator, at immediate risk of death from the event that occurred). This does not include an AE that, if it occurred in a more serious form, might have caused death.
- 3) Persistent or significant disability or incapacity (i.e., substantial disruption of one's ability to carry out normal life functions).
- 4) Hospitalisation: regardless of length of stay, even if the hospitalization is a precautionary measure for continued observation. Hospitalisation (including inpatient or outpatient hospitalization for an elective procedure) for a pre-existing condition that has not worsened unexpectedly does not constitute a serious AE.
- 5) An important medical event (that may not cause death, be life threatening, or require hospitalization) that may, based upon appropriate medical judgment, jeopardize the subject and/or require medical or surgical intervention to prevent one of the outcomes listed above. Examples of such medical events include allergic reaction requiring intensive treatment in an emergency room or clinic, blood dyscrasias, or convulsions that do not result in inpatient hospitalization.

## **9.2 Adverse Events Assessment**

For every adverse event (AE), an assessment of the relationship of the event to the administration of the vaccine will be undertaken. A related AE refers to an AE for which there is a possible, probable or definite relationship to administration of a vaccine. The investigator will make interpretation of the causal relationship of the intervention to the AE in question. This interpretation will be based on the type of event, the relationship of the event to the time of vaccine administration,

## CONFIDENTIAL

and the known biology of the vaccine. The following are guidelines for assessing the relationship of administration of the study vaccine to the AE:

1. NO RELATIONSHIP:

- No temporal relationship to study product; and
- Alternate aetiology (clinical state, environmental or other interventions); and
- Does not follow known pattern of response to study product

2. POSSIBLE:

- Reasonable temporal relationship to study product; or
- Event not readily produced by clinical state, environmental or other interventions; or
- Similar pattern of response to that seen with other vaccines

3. PROBABLE:

- Reasonable temporal relationship to study product; and
- Event not readily produced by clinical state, environment, or other interventions or
- Known pattern of response seen with other vaccines

4. DEFINITE:

- Reasonable temporal relationship to study product; and
- Event not readily produced by clinical state, environment, or other interventions; and
- Known pattern of response seen with other vaccines

Every AE observed or reported from the day of MVA.HIVA injection through to the end of the trial will be recorded on the appropriate CRF.

All AEs will be followed until resolution of the signs or symptoms or laboratory changes occurs, or until a non-study related causality is assigned.

### Serious Adverse Event (SAE) Reporting

In order to comply with current regulations on serious adverse event reporting the investigator pledges to document accurately the event, to respect notification deadlines, to provide the Sponsor with all necessary information and, if requested by the Sponsor, to give access to source documents. All SAEs will be reported by telephone, or email or fax to the Sponsor and Local Safety Monitor within one working day (24 hours) of the investigator becoming aware of the SAE occurrence.

Unexpected SAEs that are, in the opinion of the Principal Investigator or designated research physician, related to the administration of any of the research procedures should be reported to the local and OXTREC Ethics Committees and the Gambia Medicines Board within 15 calendar days of the PI becoming aware of the event. If the event is fatal or life threatening, the event should be reported within 7 calendar days.

## **CONFIDENTIAL**

Minimum details to be given in a telephone report are:

- Name of reporting doctor and contact telephone number.
- Study number.
- Nature of adverse event.
- Subject details (number, initials, sex, date of birth, weight and age).
- Date and time of event.
- Date and time of MVA.HIVA administration and dose.
- Other drug history.
- Other relevant history.
- Outcome.
- Causality.

The event will be documented on the SAE page of the CRF and reported to the Sponsor, Local Safety Monitor, DMEC, relevant Ethics Committees, Gambia Medicines Board, TSC, collaborators and funding agency as appropriate.

After the local ethics committee's response to the SAE report is received, the Sponsor, Principal Investigator, Local Safety Monitor and available co-investigators will communicate to determine the future plan for the study, which could involve amending the protocol, discontinuing the vaccinations, or continuing unchanged for the other volunteers.

**A suspected unexpected serious adverse reaction (SUSAR)** is different from an SAE in that it is unexpected and thought to be related to the study vaccine. If an unexpected adverse reaction to the trial vaccine is suspected, the Sponsor will comply with the regulatory requirements on reporting SUSARs.

